#### Demographics

We will collect age, sex, length, weight, type of surgery (UKA/TKA), side of surgery (left/right), length of stay, working hours per week, working days per week, physical nature of the job, preoperative sick-leave days, breadwinner, being self-employed, comorbidities, and complications after surgery.

### Study intervention

The following BAAS work-directed care is offered to the patient, which was proven feasible (Additional file 1: Appendix I) [13]. The orthopedic surgeon provides information before surgery about returning to work after surgery in terms of expected time to RTW and the known prognostic factors like female gender, affirmative patient-reported work-relatedness of knee symptoms, high physical work demands, high Body Mass Index (BMI), and prolonged preoperative sick absence from work [39, 40]. Next, the orthopedic surgeon refers the patient to the MCM for a preoperative examination. During this preoperative examination, the patient fills out several questionnaires (WORQ, KOOS, CSI, WAS and iPCQ; Table 1) so the MCM gains insight in the preoperative status of the patient (Fig. 1). Then, the patient is subjected to performance-based physical tests to evaluate the functional capacity, namely a floor-to-waist lifting test and functionality tests, including the DEMMI, FTST, 30-STST, and 6MWT. During this preoperative examination, the patient is given information about the perioperative care and has the opportunity to ask questions about the recovery trajectory. The findings of the preoperative examination are used as baseline measurements for setting goals in the postoperative rehabilitation and as reference values for postoperative recovery. Next, the patient receives an accelerometer (PAM 2.0), including the option of feedback from the software application Atris (Peercode B.V.) during the preoperative examination. The movement data is accessible for the patient, the primary care physical therapist, and the MCM. A week later, the MCM calls the patient to discuss the current physical activity assessed by the accelerometer and give advice on the preferred physical preoperative preparation. For example, patients are advised to train functional movements required after surgery, such as walking with a walking aid, or are advised to maintain or increase the current physical fitness level by adhering to the WHO’s latest physical activity guideline [41]. The MCM then contacts the occupational physician to inform him or her about the participation of the patient in this clinical pathway. The patient is advised to consult the occupational physician before surgery. Then, the patient is referred to the occupational case manager (OCM; occupational assessor) by the MCM, to compile a report of beneficial and limiting factors regarding RTW after KA.

During the hospitalization, the patient receives perioperative care as usual according to the KA fast track principles in both hospitals [42]. At NS hospital, patients who have decided to have KA receive an Oxford uncemented Partial Knee (Zimmer Biomet), NexGen LPS-Flex or CR Total KA (Zimmer Biomet) or Medial Rotation Knee total knee replacement (BdH Medical BV) or SAIPH Knee System (BdH Medical BV). At ETZ hospital, patients who have decided to have KA receive a SIGMA Total Knee System (Johnson and Johnson) or an Oxford Partial Knee (Zimmer Biomet).

In both hospitals, patients will receive physical therapy according to usual care while being hospitalized for two or three times a day, with the goal of gaining independence in activities of daily living such as walking, transfers in and out of bed or chair, and walking up and down stairs if necessary [43]. Also, the orthopedic surgeon and physical therapist motivate the patient to train range of motion of the knee to at least full extension (0 degrees) and 90 degrees of flexion. After hospitalization, the patient receives physical therapy from a primary physical therapy setting according to the patient’s preferences and taking into account the Royal Dutch Society for Physiotherapy (KNGF) guidelines for knee osteoarthritis [44]. The physical therapist is informed that the patient is participating in BAAS care pathway, and informed about the content of this pathway through an information letter. A work-related therapy goal is set up from the start of the therapy and monitored every six weeks throughout the whole clinical care pathway using Goal Attainment Scaling (GAS, Fig. 1) by the MCM. Progress in recovery is evaluated through questionnaires (WORQ, KOOS, and CSI), functional capacity test (floor-to-waist lifting test), functional tests (DEMMI, FTST, and 6MWT) and the physical activity level measured by the accelerometer (Table 1). The questionnaires and functional capacity evaluations tests are repeated at 6 weeks and every 3 months after surgery (Fig. 1), with the exception of the floor-to-waist lifting test at six weeks after surgery due to patient safety reasons. Data from the accelerometer is evaluated by the MCM on a weekly basis. Stop criteria for the BAAS clinical pathway are full RTW or, if RTW was not achieved after one year.

An interdisciplinary consultation is held the fourth or fifth week after surgery. The patient, the primary care physical therapist, the MCM, OCM, and occupational physician are invited to participate (Fig. 1). During this consultation, the progress, the attainment of the GAS goal, and RTW plan according to the Dutch Gatekeeper Improvement Act are discussed. If the patient has a job which he or she probably cannot return to, for example because of high knee demands due to prolonged kneeling and squatting, the possibility of work adaptions or even the topic of finding a less physically strenuous job are discussed (Fig. 1). The interdisciplinary consultation is continued if required, for instance based on unfavorable recovery data. If, after three months a delayed recovery is seen based on the patient’s experience and expert opinions of the MCM, OCM, and occupational physician, and supported by questionnaires, functional capacity evaluations and accelerometer data, the patient is referred to a multidisciplinary rehabilitation assessment (Fig. 1). Here, the patient is examined by a rehabilitation physician, occupational medicine specialist, physical therapist, and psychologist to assess barriers for delayed recovery and RTW, and whether the patient is eligible for an interdisciplinary vocational rehabilitation program. If so, the patient receives this interdisciplinary rehabilitation program [45].

The MCM from NS hospital, who is experienced in fulfilling the task of MCM through the previously performed feasibility study, will train two physical therapists working in ETZ. These physical therapists perform the tasks of an MCM in their hospital. Also, the MCMs of ETZ will be trained to perform all functional tests. Every two weeks a digital consultation will be held between all MCMs to discuss progress of the study and any questions that have arisen during the entire study period.

### Data collection

For the effectiveness study, both date of surgery and RTW data are collected by the MCM. In addition to the RTW data, the preoperative data and health surveillance data (Fig. 1) are collected in the same file by the same MCM.

### Data management

For this study, data will be coded and collected in a password-protected Microsoft Excel file. A separate Excel file will refer to the coded data of individual patients that is only accessible by the MCM.

### Statistical methods

#### Effectiveness

The effect of the BAAS care pathway on time to RTW will be statistically tested using survival analysis and gamma regression analysis including bootstrapping using R (version 4.1.0). Missing data will be handled by multivariate imputation using the aforementioned prognostic factors if possible [46]. For the repeated measurements on the time to RTW and/or full RTW, a mixed model will be used to test and estimate the size of the BAAS effect controlling for the following potential prognostic factors of delayed RTW, namely UKA vs TKA, primary vs revision KA, gender, BMI, physical nature of the job, preoperative sick leave, and patient-reported work-relatedness of knee symptoms. Hazard ratios including 95% confidence intervals will be calculated for the intervention group and tested against both control groups. In the absence of an empirically derived MCID, a difference of two weeks will be considered clinically relevant for first day of RTW and one week for full RTW. For interpreting the magnitude of the standard mean difference (SMD), three groups are defined: (i) small (SMD = 0 – 0.2); (ii) medium (SMD = 0.2 – 0.5) and (iii) large (SMD = 0.5–1.0) [47]. Sensitivity analyses on RTW will be performed for the two hospitals. Analyses will be conducted using both univariate and multivariate analyses to assess the effect size of the BAAS care pathway with and without controlling for variables. Lastly, because this control group is not from the same cohort as the intervention group, we will use propensity analysis (matched pairs) to correct for other confounding factors [48]. Potential prognostic factors for delayed RTW like UKA vs TKA gender, BMI, physical nature of the job, preoperative sick leave and patient-reported work-relatedness of knee symptoms will be used for patient matching. Secondary outcomes will be plotted in time and will be tested on differences between the usual care cohorts and the intervention cohort.

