## Background

Optimizing return to work (RTW) after knee arthroplasty (KA) is becoming increasingly important due to the growing incidence of KA and poor RTW outcomes after arthroplasty. The incidence of KA is predicted to rise substantially in the coming decades in countries with established market economies [1–4]. The largest increase is expected among patients of working age [5]. For instance, in 2030 the United States of America will be the first country where the majority of patients getting KA are of working age, followed by Great Britain in 2035 [3, 4]. Although outcomes regarding pain relief and improved knee function after KA are satisfactory, RTW among patients getting KA is relatively low. Prospectively reported non-RTW rates are 33% within six months after KA and 13% within 12 months in the Netherlands [6]. Also, the economic burden of knee osteoarthritis in the Netherlands is high. The average annual cost for the Dutch workforce due to sick leave for knee osteoarthritis was 26.9 million euros between 2015 and 2017 [7]. Considering the increase in the demand from patients seeking KA, the low RTW outcomes after KA, and a high economic burden, care optimization for patients getting KA with a focus on RTW is essential.

A closer collaboration between professionals in medical care (e.g. orthopedic surgeon, physical therapist) and occupational care (e.g. occupational physician) for working-age patients with KA might improve their RTW probabilities after surgery [8]. From the patient perspective, an individual tailored, integrated (health care and work-directed), comprehensive (from pre-operative to RTW) clinical pathway should preferably include integrated and coordinated care from four domains: (i) rehabilitation (e.g. physical therapy); (ii) patient support (e.g. setting proper goals); (iii) occupational support (e.g. proper build-up modified work); and (iv) medical support (e.g. more personal guidance from the hospital) [9, 10]. Unfortunately, proven effective work-directed care is currently not available for patients receiving KA [11, 12].

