### Measures

#### Primary outcomes

For the study on effectiveness, the primary outcomes are first day of RTW and/or first day of full RTW. First day of RTW is defined as: time in days from surgery to the first day of returning to work, regardless of the number of working hours or tasks performed. Full RTW is defined as: time in days from surgery to the first day a patient works the number of hours stated in his or her employment contract regardless of the tasks performed. For self-employed patients, full RTW is defined as: the first day of the week a patient works the number of hours equal to the number of hours he or she worked before surgery. For the first days to RTW the prospective Expect to Work study by Van Zaanen et al. will be used as usual care cohort, and for full RTW the ACTIVE trial comparison group by Straat et al. will be used [17, 18]. Test–retest reliability, minimal clinical importance difference, and minimal detectable difference of self-reported RTW are not described in the medical literature, if we are not mistaken. The effectiveness study of BAAS will be reported according to the Strengthening the Reporting of Observational Studies in Epidemiology (STROBE) guidelines [19].

For the economic evaluation, the primary outcomes are the total costs of the intervention, and the societal and health care cost obtained by a cost-questionnaire at 3, 6, 9 and 12 months according to the guidelines of the Dutch Health Care Institute (Zorginstituut Nederland), in line with the study performed by Straat et al. [17, 20]. The economic evaluation will be reported according to the Consolidated Health Economic Reporting Standards 2022 (CHEERS 2022) and we will use the human-capital method [21].

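### The covariate-adjusted BAAS effect on time to RTW is assigned to a repeated-measurements mixed model, although each patient has one, possibly censored, event time per outcome

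*Protocol article*

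**What the plan says.** **Outcomes.** The Primary outcomes section defines first RTW as "time in days from surgery to the first day of returning to work, regardless of the number of working hours or tasks performed" and full RTW as "time in days from surgery to the first day a patient works the number of hours stated in his or her employment contract", with an analogous first-day definition for the self-employed. Each patient therefore has one value per outcome.

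**Analyses.** Under Statistical methods, Effectiveness, time to RTW is to be "statistically tested using survival analysis and gamma regression analysis including bootstrapping". A mixed model follows: "For the repeated measurements on the time to RTW and/or full RTW, a mixed model will be used". This model is given both the test and the estimate of the BAAS effect, adjusted for seven listed prognostic factors. The next sentence of the section reads: "Hazard ratios including 95% confidence intervals will be calculated for the intervention group and tested against both control groups". Univariate and multivariate analyses and, last, a matched-pairs propensity analysis are added. None is named as primary, although Study design presents matched pairs as the comparison for effectiveness.

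**Relevance.** The same section sets a clinically relevant difference of two weeks for first RTW and one week for full RTW.

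**Incomplete outcomes.** "Missing data will be handled by multivariate imputation using the aforementioned prognostic factors if possible". Study intervention ends the pathway at full RTW, or at one year if RTW has not been reached. The Background reports: "Prospectively reported non-RTW rates are 33% within six months after KA and 13% within 12 months in the Netherlands".

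**The concern.** A mixed model for repeated measurements needs several observations of the same outcome per patient. Time to a first event gives one. This model is nevertheless the one that is to test and size the BAAS effect with covariate adjustment. In ordinary form it also has no term for a patient whose time is known only to exceed 12 months, and it does not produce the hazard ratios named in the next sentence.

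A second problem follows. The method that does handle censoring, survival analysis, is tied in the text only to hazard ratios. A hazard ratio cannot be set against a threshold of one or two weeks. A reader who wants the verdict in weeks is led to the gamma or the mixed model. If either is fitted in ordinary form to patients with an observed date, the patients with the poorest outcome drop out and the difference shrinks. The document has a rule for missing data but does not say that a patient known not to have returned is censored rather than missing.

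**Working it through.** **1. Model against outcome.** Primary outcomes gives one number per patient for first RTW and one for full RTW. Effectiveness speaks of repeated measurements on these times. The two statements cannot both hold. What is measured repeatedly is the set of secondary questionnaires and functional tests (Table 1, baseline to 12 months). A random effect for hospital or matched pair could be a reason for a mixed-effects survival model, but the reason given is repeated measurement.

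**2. How much censoring to expect.** At 13% not returned by 12 months, the minimum sample gives 0.13 × 125 = 16.25 and the planned sample 0.13 × 150 = 19.5. That is about 16 to 20 BAAS patients without an event time if BAAS did no better than usual care.

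**3. What leaving them out would do.** The plan gives no figure for this, so it is an illustration under assumptions.

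Inputs from the Background: usual-care non-return S(26) = 0.33 and S(52) = 0.13, with time in weeks. Assumed: the shape of the distribution (lognormal or Weibull), and that BAAS multiplies every time by a factor *a*.

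Fits:
- Lognormal: σ = ln 2 / (1.126 − 0.440) = 1.010; μ = ln 26 − 1.010 × 0.440 = 2.814.
- Weibull: k = ln[ln(1/0.13) / ln(1/0.33)] / ln 2 = 0.880; λ = 26 / [ln(1/0.33)]^(1/k) = 23.12.

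Both return 0.33 and 0.13 by construction.

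Quantities, by numerical integration:
- Restricted mean, R = ∫ S(t) dt from 0 to 52. This keeps the censored patients.
- Mean among returners, M = [R − 52·S(52)] / [1 − S(52)].

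Example, lognormal usual care: R = 21.93 and M = (21.93 − 6.76) / 0.87 = 17.44. With a = 0.9: S(52) = 0.109, R = 20.36, M = 16.48. Difference in R = 1.57 weeks; difference in M = 0.96 weeks.

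| Shape | a | Difference in R (weeks) | Difference in M (weeks) |
|---|---|---|---|
| Lognormal | 0.90 | 1.57 | 0.96 |
| Weibull | 0.90 | 1.46 | 0.69 |
| Lognormal | 0.85 | 2.40 | 1.48 |
| Weibull | 0.85 | 2.23 | 1.08 |
| Lognormal | 0.80 | 3.27 | 2.03 |
| Weibull | 0.80 | 3.05 | 1.50 |

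At a = 0.90 the returners-only figure falls below one week while the restricted-mean figure lies above it. At a = 0.85 the same happens at two weeks. At a = 0.80 the two-week line is crossed under the Weibull but not under the lognormal.

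**The case against.** The strongest reply is that a suitable method is already in the plan. Survival analysis is named first and hazard ratios with intervals are to be reported, so patients not back at 12 months have a place. That stands. It would be wrong to infer that the plan has no valid way to treat censored patients.

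A reader might go further and infer that non-returners will be dropped or imputed. The text does not say so. The imputation sentence concerns missing data and never classes non-return as missing. The bias shown above is a risk left open, not a stated rule. Nor is gamma regression wrong in itself: it suits a positive, skewed time and fails here only if fitted without a censoring term, which the article does not specify. Such detail may sit in an analysis plan that is not shown.

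It can also be said that survival curves give medians in weeks, and that adjustment is planned elsewhere through the multivariate analyses. Both are fair. An estimate in weeks is obtainable, but the article does not say that it will be taken from the survival analysis.

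The illustration has limits. The 33% and 13% come from a published Dutch study, not from either comparator cohort. The Background does not say whether they refer to any or to full RTW; the Discussion cites 49% taking more than six months to full RTW from the same source, so censoring for that outcome may exceed 13%.

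None of this rescues the mixed-model sentence. It is a stated analysis that contradicts the outcome definitions, not a detail left for later.

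**Conclusion.** The point holds in a limited form. The mixed model for time to RTW does not fit the outcome and should not carry the adjusted effect estimate. Beside it, the plan judges relevance in weeks, names only the hazard ratio for its censoring-aware method, and states an imputation rule without a censoring rule.

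The possible size is about 0.6 to 0.8 weeks lost at a 10% acceleration (1.57 − 0.96 = 0.61; 1.46 − 0.69 = 0.77), enough to change a verdict against one week. This depends on the assumed distributions and acceleration, on the quoted non-return rates applying, and on an estimate in weeks being taken from returners only, which the document does not say will happen.

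**What to change.** - Delete the mixed model for time to RTW. Keep mixed models for the secondary measures taken at several time points.
- For each outcome, name one primary analysis in the sample matched to its own comparator cohort that handles censoring and yields weeks. One choice is the difference in restricted mean time to RTW up to 52 weeks, or up to the longest follow-up common to both cohorts, with a pair-level bootstrap confidence interval. Read it against the two-week or one-week threshold, and support it with a Cox hazard ratio adjusted for the listed factors.
- State that patients known not to have returned are censored at 12 months and that those lost are censored at last contact.
- Limit imputation to covariates and to unknown dates of a return known to have occurred. A ban on all imputation would go too far.
- Fit any gamma model as a parametric survival model with censoring, as a sensitivity analysis.

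**Cost:** wording and a few lines of R. No further BAAS data are needed, but the follow-up length in both comparator cohorts must be checked because it sets the horizon. The restricted mean must state that horizon, and censoring at last contact assumes that loss is non-informative, which matters with 20% loss expected.

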### Participants

#### Sample size

A minimal required sample size was calculated using R (version 3.6.3) with a power of 0.8 and a significance level of 0.05. The effect size was calculated with a mean difference of two weeks in comparison to a Dutch study on RTW after KA [15]. With a calculated minimal required sample size of 125 and an expected loss to follow-up of 20%, we intend to include 150 patients (75 in NS and 75 in ETZ).

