In transition processes, in which care as usual is replaced by a new care pathway, the essential role of the patients and health care professionals is often overlooked. Therefore, in our study the professionals involved in the care transitions in the two hospitals will collect and scrutinize the data together and, based on the results, determine what kind of action should be performed to enhance RTW in close contact with the patient. One of the consequences of this iterative cycle will be that all professionals as well as the patients involved become partners in achieving an optimal RTW. This way, the embedded scientist who, in daily practice, collects, creates, and reviews knowledge, and investigates the effectiveness of this newly implemented care pathway is an essential actor in creating and implementing future RTW pathways for other groups of working age patients.

Lastly, by using the data from two Dutch cohorts on RTW with similar inclusion criteria, our study is designed to be more cost-effective than a randomized controlled trial.

The limitations of this study protocol are that the lead author has an active role as an MCM in this study. This is why we included patients from a second hospital (ETZ). Also, we will not perform an RCT. We will use the data from two other prospective cohort studies with similar inclusion criteria to compare our findings to usual care. The care for knee arthroplasty is, fortunately, largely standardized in the Netherlands [44, 53]. Also, we will use propensity analysis to reduce the bias due to possible differences between our cohorts and the two comparison cohorts [17, 18].

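### The return-to-work comparison names no preoperative WORQ, KOOS, CSI or WAS score for adjustment or matching, so a residual baseline difference between cohorts may be credited to BAAS

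*Protocol article*

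**What the plan says.** Protocol article, Statistical methods, Effectiveness: the model for the BAAS effect is specified as "controlling for the following potential prognostic factors of delayed RTW, namely UKA vs TKA, primary vs revision KA, gender, BMI", followed by physical nature of the job, preoperative sick leave and patient-reported work-relatedness of knee symptoms. The word *namely* closes this list. The propensity-matching sentence in the same section repeats these factors without primary versus revision, but introduces them with *like*, so it is not strictly closed.

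Study intervention: at the preoperative examination "the patient fills out several questionnaires (WORQ, KOOS, CSI, WAS and iPCQ; Table 1"). The stated uses of the findings are goal setting and reference values for recovery. Use as covariates is not mentioned.

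The usual-care groups are external: Expect to Work for first RTW and the ACTIVE comparison group for full RTW. The Discussion gives the safeguard: "we will use propensity analysis to reduce the bias due to possible differences between our cohorts and the two comparison cohorts". The Effectiveness section also says: "Secondary outcomes will be plotted in time and will be tested on differences between the usual care cohorts and the intervention cohort".

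**The concern.** Without randomisation, the credibility of the RTW estimate rests on which baseline variables enter the regression and the propensity model. Difficulty with knee-straining work (WORQ), self-rated work ability (WAS), knee symptoms and function (KOOS) and sensitisation (CSI) are plausible confounders of time to RTW. For BAAS patients they are already recorded before the accelerometer, the case manager's advice call and the occupational referral, so they are baseline values and not consequences of those components.

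Matching and regression directly control only what enters them. The propensity step is presented as dealing with further confounding, yet it names no factor beyond those in the regression. If BAAS patients start with better work ability than the listed factors reveal, they will return sooner with no pathway effect. If they start worse, a real effect is masked. An analysis plan that follows the closed list would inherit the omission, and scores added after the RTW data are seen would look data-driven.

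**Working it through.** The plan gives no figure for this choice, so arithmetic can only illustrate its possible size. The gap, the association and the correlation below are assumptions.

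**The plan's own figures.** The Sample size section uses power 0.8 and significance level 0.05. On the effect it says: "The effect size was calculated with a mean difference of two weeks in comparison to a Dutch study on RTW after KA". Its results are 125 patients required and 150 to be included, allowing for 20% loss. No SD is stated, so 125 cannot be reproduced. The SD that it implies depends on the design assumed (two-sided test, 1.96 + 0.84 = 2.80):
- 125 in total, two groups: 2 × √(62.5/2) / 2.80 = 3.99 weeks
- 125 per group: 2 × √(125/2) / 2.80 = 5.64 weeks
- 125 in a one-sample or paired test: 2 × √125 / 2.80 = 7.98 weeks

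The plausible SD on the plan's own terms is therefore about 4 to 8 weeks. After 20% loss, 150 × 0.8 = 120 patients remain.

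**Hazard-ratio scale.** Inputs: 120 per group (equal matched groups assumed), and 87% returned by 12 months (from the 13% non-RTW in the Background).
- SE(log HR) = √(4 / (0.87 × 240)) = 0.138
- Bias in log HR = b × g, where b is the log-hazard per SD of the omitted score left after the listed covariates, and g is the residual cohort gap in SDs
- False-positive rate = Φ(bias/SE − 1.96) + Φ(−bias/SE − 1.96)

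| b | g | Bias | HR under no effect | False-positive rate |
|---|---|---|---|---|
| 0.2 | 0.2 | 0.04 | 1.04 | 6.0% |
| 0.3 | 0.3 | 0.09 | 1.09 | 10.0% |
| 0.4 | 0.5 | 0.20 | 1.22 | 30.4% |

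**Weeks scale.** Bias = g × r × SD, where r is the correlation of the omitted score with time to RTW after the listed covariates.

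| g | r | SD 3.99 | SD 5.64 | SD 7.98 |
|---|---|---|---|---|
| 0.3 | 0.3 | 0.36 | 0.51 | 0.72 |
| 0.5 | 0.3 | 0.60 | 0.85 | 1.20 |
| 0.5 | 0.4 | 0.80 | 1.13 | 1.60 |

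The plan's relevance thresholds are one week for full RTW and two weeks for first RTW. The middle case (first row) is below both. In this grid only a 0.5 SD gap passes one week: at the largest SD when r is 0.3, and from 5.64 weeks upward when r is 0.4. No case reaches two weeks.

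**The case against.** The covariate list has a reasoned source. Study intervention names five known prognostic factors with citations: gender, work-relatedness, physical demands, BMI and preoperative sick absence. The Effectiveness section carries all five forward and adds implant type and revision status. No section calls a preoperative WORQ, KOOS, CSI or WAS score prognostic for RTW. This explains the list, but it does not justify leaving collected baseline scores out of a non-randomised comparison.

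Four stronger readings are tempting, and the documents do not support them.
- A reader might infer that nothing in the lists reflects preoperative work limitation. Preoperative sick leave does so directly, and job demands and work-relatedness do so in part. Only a residual gap can bias the result.
- A reader might infer that both lists shut the scores out. The regression list does. The matching list opens with *like* and leaves room.
- A reader might take the delayed-recovery rule, "supported by questionnaires, functional capacity evaluations and accelerometer data", as the protocol's own evidence that T0 scores predict RTW. That rule applies three months after surgery, and the Discussion's remark on sensitisation concerns patients after KA. Both describe postoperative monitoring.
- A reader might infer from the planned tests of secondary outcomes that the control cohorts hold all four scores at baseline. The sentence implies that they hold some measures, but it names neither instrument nor time point. It says least about WAS, which is absent from the follow-up questionnaires listed in Study intervention.

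**Conclusion.** The point stands in limited form. The adjustment list is closed and the matching list, though not strictly closed, names no preoperative function or work-ability score, while BAAS patients have four such scores. A cohort difference that sick leave, job demands and work-relatedness do not capture may be attributed to BAAS. It cannot be said that a gap exists or that the result will be biased.

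With moderate assumed inputs the distortion is modest: a hazard ratio of 1.09 with a false-positive rate near 10%, or about 0.4 to 0.7 weeks. It becomes material for the one-week full-RTW threshold only with a residual gap of about 0.5 SD. How far it can be corrected depends on which T0 scores each control cohort holds, and the article does not say. The change is still worth making, because covariate control is this design's only safeguard against cohort differences.

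**What to change.** In Statistical methods, Effectiveness, amend both lists separately for each control cohort (Expect to Work for first RTW, ACTIVE for full RTW):
- Add to the RTW regression and to the propensity model those T0 scores that both that cohort and BAAS hold: WORQ first, then KOOS, CSI and WAS.
- Report standardised differences for these scores before and after matching.
- Where a control cohort holds no such T0 score, state that its RTW comparison is not controlled for preoperative function or work ability, and add a sensitivity analysis for unmeasured confounding, for example over a range of assumed gaps and associations as above.

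This should be fixed before the RTW data are compared. It costs a change of wording and up to four more covariates, with no new data collection. The downside is small: T0 scores missing in some patients need the imputation already planned, and slightly fewer close matches may be found.
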